## Abstract

**Background:**

Posttraumatic osteoarthritis can develop after an intra-articular extremity fracture, leading to pain and loss of function. According to international guidelines, anatomical reduction and fixation are the basis for an optimal functional result. In order to achieve this during fracture surgery, an optimal view on the position of the bone fragments and fixation material is a necessity. The currently used 2D-fluoroscopy does not provide sufficient insight, in particular in cases with complex anatomy or subtle injury, and even an 18-26% suboptimal fracture reduction is reported for the ankle and foot. More intra-operative information is therefore needed.

Recently the 3D-RX-system was developed, which provides conventional 2D-fluoroscopic images as well as a 3D-reconstruction of bony structures. This modality provides more information, which consequently leads to extra corrections in 18-30% of the fracture operations. However, the effect of the extra corrections on the quality of the anatomical fracture reduction and fixation as well as on patient relevant outcomes has never been investigated.

The objective of this study protocol is to investigate the effectiveness of the intra-operative use of the 3D-RX-system as compared to the conventional 2D-fluoroscopy in patients with traumatic intra-articular fractures of the wrist, ankle and calcaneus. The effectiveness will be assessed in two different areas: 1) the quality of fracture reduction and fixation, based on the current golden standard, Computed Tomography. 2) The patient-relevant outcomes like functional outcome range of motion and pain. In addition, the diagnostic accuracy of the 3D-RX-scan will be determined in a clinical setting and a cost-effectiveness as well as a cost-utility analysis will be performed.

**Methods/design:**

In this protocol for an international multicenter randomized clinical trial, adult patients (age > 17 years) with a traumatic intra-articular fracture of the wrist, ankle or calcaneus eligible for surgery will be subjected to additional intra-operative 3D-RX. In half of the patients the surgeon will be blinded to these results, in the other half the surgeon may use the 3D-RX results to further optimize fracture reduction. In both randomization groups a CT-scan will be performed postoperatively. Based on these CT-scans the quality of fracture reduction and fixation will be determined. During the follow-up visits after hospital discharge at 6 and 12 weeks and 1 year postoperatively the patient relevant outcomes will be determined by joint specific, health economic and quality of life questionnaires. In addition a follow up study will be performed to determine the patient relevant outcomes and prevalence of posttraumatic osteoarthritis at 2 and 5 years postoperatively.

**Discussion:**

The results of the study will provide more information on the effectiveness of the intra-operative use of 3D-imaging during surgical treatment of intra-articular fractures of the wrist, ankle and calcaneus. A randomized design in which patients will be allocated to a treatment arm during surgery will be used because of its high methodological quality and the ability to detect incongruences in the reduction and/or fixation that occur intra-operatively in the blinded arm of the 3D-RX. An alternative, pragmatic design could be to randomize before the start of the surgery, then two surgical strategies would be compared. This resembles clinical practice better, but introduces more bias and does not allow the assessment of incongruences that would have been detected by 3D-RX in the blinded arm.

**Trial registration:**

Dutch Trial Register NTR 1902

## Background

Fractures of the extremities are common injuries, with an incidence of 38 wrist fractures per 10,000 inhabitants per year,[1] and an estimate of 25,000 - 68,000 ankle fractures per year in the Netherlands [2]. Posttraumatic osteoarthritis can develop after an intra-articular extremity fracture, which can lead to pain and loss of function. According to international guidelines anatomical reduction and fixation are the basis for an optimal functional result [3]. This can be achieved by closed reduction and cast fixation. If a conservative treatment leads to a suboptimal reduction and fixation, surgical treatment is indicated.

During open reduction and internal fixation (ORIF) conventional 2D-fluoroscopy is used to gain more insight in the fracture fragments and fixation material next to a direct view. When it involves complex anatomy or subtle injury 2D-fluoroscopy often underestimates the extent of the injury or the degree of displacement of fracture fragments, which can be misleading to the surgeon. Consequently, postoperative X-ray images and CT-scans frequently show incorrect positioned screws or incongruences, like gaps and step-offs, in the joint surface, while these were not recognized on the intra-operative 2D-fluoroscopic images. E.g. for the ankle and foot even an 18-26% suboptimal fracture reduction is reported [4-6]. More intra-operative information is therefore needed in order to minimize suboptimal fracture reduction.

Recently a 3-Dimensional Rotational X-ray system (3D-RX-system) was developed which can provide more detailed imaging intra-operatively. This system consists of a mobile C-arm unit modified to provide a motorized rotational movement and is combined with a workstation. Next to conventional 2D-fluoroscopy this system can provide multiplanar 3-dimensional reconstruction of the osseous structures.

Several cadaveric studies have been performed on different joints of the upper and lower limb to evaluate the image quality of intra-operative 3D-imaging [7-12]. In these studies 3D-imaging had a better diagnostic value than conventional radiography and 2D-fluoroscopic images. Although the subjective imaging quality was higher in CT-scanning, images of the intra-operative 3D-imaging were comparable in diagnostic value. In addition, in some clinical studies concerning intra-operative 3D-imaging, this modality has shown to provide extra information. Extra corrections after 3D-imaging were performed in 11-30% of the fracture operations [11,13-17]. These corrections concerned suboptimal fracture reduction, like intra-articular steps-offs and fracture gaps, and incorrectly positioned fixation material.

The studies mentioned above have shown that intra-operative 3D-imaging provides additional information and allows the surgeon to recognize problems with fracture reduction and/or fixation during the operation. However, these studies used indirect measurements to establish the added value of intra-operative 3D-imaging. The direct effects on the quality of fracture reduction and fixation and patient relevant outcomes have not yet been investigated.

The aim of this protocol for a randomized clinical trial is to investigate the effectiveness of the the intra-operative use of the 3D-RX-system as compared to the use of conventional 2D-fluoroscopy alone in patients with traumatic intra-articular fractures of the wrist, ankle and calcaneus. This effectiveness will be assessed in two different areas: 1) the quality of fracture reduction and fixation, based on the current golden standard, Computed Tomography. 2) The patient-relevant outcomes like functional outcome, range of motion and pain. In addition, the diagnostic accuracy of the 3D-RX-scan will be determined in a clinical setting and a cost-effectiveness as well as a cost-utility analysis will be performed.

### Choice for the study design

With this study we aim to address multiple issues regarding the intra-operative use of 3D-imaging in fractures of the extremities; the diagnostic value (sensitivity and specificity) of the 3D-RX-scan in a clinical setting, the therapeutical outcome and its effect on the quality of fracture reduction and fixation and the patient relevant outcomes. For this purpose we prefer a blinded randomized design, offering the most robust way to investigate the effect of the intra-operative use of 3D-imaging. In order to compare both techniques, patients will be randomized during surgery after the definitive adjustments on the basis of 2D-fluoroscopy and before 3D-fluoroscopy. This avoids the phenomenon that the surgeon neglects the 2D-fluoroscopy and relies on the envisioned 3D-images for the reduction and fixation later during the surgical procedure. An additional advantage of this design is that both the diagnostic value as well as the effects on the quality of fracture reduction and fixation can be investigated.

A disadvantage of our study design is that half of the patients receive radiation of the 3D-scan, while they cannot benefit from this 3D-scan. Because of the relatively low radiation dose of the 3D-scan, this disadvantage is considered acceptable.

An alternative, more pragmatic, study design would randomize between two operative strategies: with or without intra-operative 3D-imaging. In this design no patient would receive unbeneficial radiation doses and this set-up will probably be a better reflection of the clinical practice. However, comparing two surgical strategies does not allow the assessment of any missed incongruences when using 2D-fluoroscopy alone. In addition, when the surgeon knows he can employ the 3D-imaging strategy, he might change his attitude towards 2D-fluoroscopy and be less accurate. Hence, more bias will be introduced because of the surgeon's attitude towards 3D-imaging. In addition, 3D-imaging may also detect incongruences that are corrected, but may not have any influence on functional outcomes or long-term development of posttraumatic osteoarthritis. This possible overdiagnosing with 3D-imaging cannot be detected with a pragmatic design.

The choice for our study design induced some practical drawbacks, i.e. the blinding of the 3D-scan for the surgeon needs some discipline as the only way to blind the 3D-scan is to turn the screens from the surgeon. In addition this design warrants more administration during surgery because the surgeon evaluates the radiological results after every imaging modality. Because of the use of a secured internet module, this administration is relatively simple.

## Methods/design

### Objectives

The objectives of this randomized clinical trial are to:

1. Assess the quality of fracture reduction and fixation based on the postoperative CT-scans of the ankle, calcaneus, or wrist, determined by a standard scoring protocol

2. Assess the patient relevant outcomes

3. Assess the diagnostic value of an intra-operative 3D-RX-scan in a clinical setting

4. Perform a cost-effectiveness analysis to assess whether the use of 2D-fluoroscopy and the 3D-RX-scan eventually results in cost savings or is compensated for by increased health benefits in comparison with the use of 2D-fluoroscopy only

### Study population

The study population consists of adult patients with a traumatic intra-articular fracture of the wrist, ankle or calcaneus in which operative treatment is indicated.

Inclusion criteria are:

• Adult patients (age > 17 years)

• Distal radius fracture, AO-classification A2-C3, or

• Distal tibial fracture, AO-classification B1-C3, or

• Malleolar fractures, AO-classification A1-C3, or

• Calcaneal fractures, Sanders classificationI-IV

• Fracture surgery (ORIF or CRIF) required (i.e. intra-articular fractures with dislocation).

Only intra-articular fractures will be included in this trial, because the additional value of intra-operative 3D-imaging is to be expected in these types of fractures. The complexity of these fractures warrants more insight in the fracture fragments and fixation material than in extra-articular fractures. It is debatable whether the distal radius fractures AO-classification A2-3 and malleolar fractures C1-3 are true intra-articular fractures. Since we are interested in the congruence of the distal radioulnar joint (DRUJ) and the tibiofibular syndesmosis, these fracture types will be included. Especially in these fracture types, 3D-imaging can give more insight in rotation or subluxation of the ulna or fibula in these articulations.

Exclusion criteria are:

• Pathological fractures, i.e. due to underlying malignant disorder

• Rheumatoid osteoarthritis

• No written informed consent

• Inability to understand trial features due to mental handicap or language problems

• Pregnancy

### Study design

The EF3X-trial is an international randomized multicenter trial, with participation of 4 hospitals (3 university hospitals and 1 regional hospital). Patients eligible for operative treatment of their intra-articular fracture of the wrist, ankle or calcaneus will be randomized after the surgeon is satisfied with the reduction and fixation after 2D-imaging. Patients will be blinded for the availability of the 3D-scan.

When operative treatment is indicated in patients presenting to the Emergency Department (ED) with an intra-articular fracture of the wrist, ankle or calcaneus, they will be counselled and asked for informed consent if the in- and exclusion criteria are met.

During surgery, initially only 2D-fluoroscopy is used for the intra-operative imaging as part of the usual intra-operative diagnostic procedure (Figure 1). The surgeon will then operate until (s)he is satisfied with fracture reduction and fixation. Then the surgeon will be asked to evaluate the conclusive 2D-images according to the scoring protocol for anatomical reduction and fixation, which is developed in the AMC. After this evaluation a 3D-RX-scan will be performed and randomization will take place.

**Figure 1 F1:**
[figure not shown]
**Flow chart of the EF3X-trial**.

The randomization will determine whether or not the information of the 3D-scan will be made available to the surgeon. Randomization is performed by an internet randomization module prepared by the AMC Clinical Research Unit. Block randomization is used and randomization will be stratified for the fractured joint (wrist, ankle or calcaneus) and participating centre. Since it is not possible to blind the surgeon, randomization takes place after the surgeon has finished operating based on the information of 2D-fluoroscopy and is ready to close the wound. In this way (s)he cannot anticipate on the likeliness (s)he gets extra information of the 3D-scan. Patients will not be informed about whether or not the 3D-scan was made available to the surgeon.

If the 3D-scan results will not be made available, the surgeon terminates the procedure. If the information of the 3D-scan is available to the surgeon he can act on the findings and, if necessary, surgical corrections can be made. If the surgeon is now satisfied with the operation result conclusive 2D-fluoroscopic images and a conclusive 3D-scan must be performed. The conclusive 3D-scan needs to be evaluated according to the scoring protocol for anatomical reduction. In both randomization groups a CT-scan will be performed postoperatively.

The follow-up visits after hospital discharge will be planned at 6 and 12 weeks and 1, 2 and 5 years postoperatively.

### Primary and secondary endpoints

Our primary outcomes are the quality of fracture reduction and fixation based on the postoperative CT-scans of the wrist, ankle or calcaneus. This will be determined by 3 independent experts. These experts will systematically evaluate the postoperative CT-scans according to a standard scoring protocol. After this evaluation the images will be classified as optimal or suboptimal. A suboptimal reduction and/or fixation will be defined as an indication for a revision following from the systematic evaluation. In addition, this classification will be based on the radiological images alone. Patient related factors, like swelling of the soft tissue will not be taken into account in this evaluation of a (sub)optimal quality of fracture reduction and/or fixation.

A standard scoring protocol for the radiological evaluation will be developed for each joint separately. Although scoring protocols for the wrist, ankle and calcaneus have been described in the literature, most of them lack clinical sensitivity, and are therefore infrequently used [18]. Another reason for not using these scoring protocols is that they merely consist of assessment of distance and angle measurements that have a high interobserver variance and are infrequently used in clinical practice [19-23]. The scoring protocols we developed are based on a Delphi consensus on how to evaluate the different joints. For the wrist and ankle this Delphi consensus was performed in the Netherlands [24]. A Delphi consensus for the calcaneus is currently being performed with international experts.

Second, the patient-relevant outcomes like functional outcome measured by joint specific questionnaires (Patient Rated Wrist Evaluation for the wrist and Foot and Ankle Outcome score and AOFAS for the ankle and calcaneus) will be determined. The patient relevant outcomes one year postoperative will be used as endpoints. Patient relevant outcomes determined at 2 and 5 years postoperatively will be used for a follow up study for the prevalence of posttraumatic osteoarthritis.

Before ending the operation, conclusive 2D-fluoroscopic images and a conclusive 3D-RX-scan are being performed. Together with the postoperative CT-scan (reference test) these radiologic images all represent the final operating result. Therefore the diagnostic value of only the conclusive 2D-fluoroscopic images and 3D-RX-scan will be determined. This will be done for the wrist, ankle and calcaneus separately. Hereby the detection of a suboptimal result, as described above, on the 2D-fluoroscopic images and/or 3D-RX-scan will be compared to the postoperative CT-scans.

A cost-effectiveness analysis will be performed to assess the relative benefit from a societal perspective of the use of the 3D-RX-scan in addition to 2D-fluoroscopy.

Our secondary study outcomes are:

> The number and type of corrections made after 2D-fluoroscopy

> The number and type of corrections made after a 3D-scan

> The number of revision operations within 30 days

> The number and type of complications within 30 days

> The length of the hospital stay expressed in days

> The quality of life measured by the SF-36

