### Data analysis

All analyses will be performed in accordance with the intention to treat principle.

The primary outcome, the quality of fracture reduction as well as the quality of fixation will be classified as optimal or suboptimal. This dichotomous outcome, will be described as a percentage in both groups. Differences between study groups will be analysed by means of a Chi-square test. A p-value < 0.05 will be taken as the threshold for statistical significance.

The scores of the functional outcomes determined by joint specific questionnaires at 1 year postoperative will be expressed as means and standard deviations (SD) in case of a normal distribution. Non-normally distributed outcomes will be expressed as medians and interquartile ranges. Normality of continuous data will be tested with the Shapiro-Wilk and Kolmogorov-Smirnov test and by inspecting the frequency distributions (histograms). The homogeneity of variances will be tested using the Levene's test. The functional outcomes will be assessed using the Student's T-test (parametric data) or the Mann-Whitney *U*-test (non-parametric data). Differences will be considered statistically significant when P-values are < 0.05.

The diagnostic accuracy of a suboptimal quality of fracture reduction and/or fixation will be determined for reduction and fixation for the wrist, ankle and calcaneus separately. Sensitivity, specificity, positive and negative predictive values for both 2D-fluoroscopy and the 3D-RX-scan will be calculated with the corresponding 95% confidence intervals for the classification of an optimal or suboptimal result as described above. This will be determined for both 2D-fluoroscopy and the 3D-RX-scan with the postoperative CT-scan as reference standard.

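### 3D-RX sensitivity is biased downward if open-arm conclusive scans, taken after 3D-guided correction, are analysed together with blinded-arm scans

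*Protocol article*

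**What the plan says.** Four statements in the Protocol article fix the accuracy analysis.

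- **Which images.** Under Primary and secondary endpoints: "Therefore the diagnostic value of only the conclusive 2D-fluoroscopic images and 3D-RX-scan will be determined". The reason given just before it is that "Together with the postoperative CT-scan (reference test) these radiologic images all represent the final operating result".
- **How it is split.** In the same section: "This will be done for the wrist, ankle and calcaneus separately". Data analysis repeats the split by joint and lists the measures: "Sensitivity, specificity, positive and negative predictive values for both 2D-fluoroscopy and the 3D-RX-scan will be calculated with the corresponding 95% confidence intervals". Neither section mentions the randomization arm.
- **Open arm** (3D result shown to the surgeon). Study design, in the text after Figure 1: "If the information of the 3D-scan is available to the surgeon he can act on the findings and, if necessary, surgical corrections can be made". It continues: "If the surgeon is now satisfied with the operation result conclusive 2D-fluoroscopic images and a conclusive 3D-scan must be performed".
- **Blinded arm.** In the same place: "If the 3D-scan results will not be made available, the surgeon terminates the procedure". The only 3D scan in this arm therefore already shows the final state.

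Every patient in both arms has a postoperative CT as reference. Randomization comes after the surgeon is satisfied with the result on 2D-fluoroscopy.

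**The concern.** Using conclusive images makes sure that the index test and the CT show the same state of the joint. It does not deal with how that state came about. In the open arm, a positive first 3D scan can lead to removal of the fault before both the analysed 3D scan and the CT. Faults that 3D shows tend to leave the set of CT-suboptimal cases, and faults that 3D misses stay in it. In the blinded arm nothing is corrected between the 3D scan and the CT.

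If the two arms go into one table per joint, part of the sensitivity denominator has been filtered by the test under study. The more consistently surgeons correct what 3D shows, the lower the apparent sensitivity of 3D. Positive and negative predictive values would also average over two prevalences of a suboptimal result, planned at 17% and 5%. At stake is the third objective, the diagnostic value of 3D-RX in a clinical setting.

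**Working it through.** **Inputs from Sample size calculation.** Suboptimal result in 17% with 2D alone and 5% with 3D-RX; two-sided α = 0.05 (two-sided is assumed), power 0.80, continuity-corrected chi-square; 122 per group; 250 per fracture type. The article gives no sensitivity, no probability that a detected fault is corrected, and no sample size for accuracy.

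**Reproducing the plan's figure.** Without correction, n = [1.96·√(2·0.11·0.89) + 0.8416·√(0.17·0.83 + 0.05·0.95)]² / 0.12² = 105.5, that is 106. With continuity correction, n = (105.5/4)·[1 + √(1 + 4/(105.5·0.12))]² = 121.6, that is 122, as stated. For dropout, 244/0.97 = 252 against 250 stated, which agrees given that the 3% is approximate.

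**Model.** Let Se be the sensitivity of 3D for faults left after 2D (the blinded-arm value) and c the probability that a detected fault is corrected. Assume that corrections succeed and create no new faults.

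1. Going from 17% to 5% requires 17·Se·c = 12, so Se·c = 12/17 = 0.706. Since c cannot exceed 1, the lowest compatible Se is 0.706.
2. Suppose the experts' reading of the repeat scan reproduces the surgeon's misses. Of the residual 5 per 100, 17·Se − 12 were seen but left, so open-arm sensitivity is (17·Se − 12)/5.
3. With equal arms, pooled sensitivity is (17·Se + 17·Se − 12)/22 = (34·Se − 12)/22.
4. The loss is Se minus this, which is (12/22)·(1 − Se).

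| Se (blinded arm) | c | Open-arm sensitivity | Pooled | Loss, points |
|---|---|---|---|---|
| 0.706 | 1.00 | 0 | 0.545 | 16.0 |
| 0.80 | 0.88 | 0.32 | 0.691 | 10.9 |
| 0.90 | 0.78 | 0.66 | 0.845 | 5.5 |
| 1.00 | 0.71 | 1.00 | 1.00 | 0 |

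**Partial persistence.** If a fraction ρ of the reading error carries over to the repeat scan and the rest is read independently, the loss is multiplied by ρ. At ρ = 0.5 it is 8.0, 5.5 and 2.7 points for Se 0.706, 0.80 and 0.90. At ρ = 0 it is nil.

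**What the blinded arm alone costs.** Expected CT-suboptimal cases per joint are 122·0.17 = 20.7 in the blinded arm and 122·0.05 = 6.1 in the open arm, 26.8 in all. At Se 0.80 the 95% half-width is 1.96·√(0.16/20.7) = 0.172 for the blinded arm, against 1.96·√(0.16/26.8) = 0.151 pooled. For specificity, the CT-optimal cases fall from 122·(0.83 + 0.95) = 217 to 122·0.83 = 101. Those intervals widen by a factor of √(217/101) = 1.47, against √(26.8/20.7) = 1.14 for sensitivity.

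**The case against.** **Pooling is not stated in so many words.** This is correct. No sentence says that the arms share one table, and a full analysis plan may separate them. The Discussion part of the Abstract and the section on the choice of design show that the authors valued the blinded arm for seeing uncorrected 3D findings. But neither restricts the accuracy analysis to that arm, and the endpoint section describes conclusive 2D and 3D images without reference to arm. Both arms together is the plain reading of what the article fixes. A narrower reading, in which the term covers only the scan that Study design calls conclusive, would leave only the open arm, with about 6 suboptimal cases per joint.

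**The readers differ.** Corrections follow the operating surgeon's reading. Accuracy, under Data collection, rests on three experts reading blinded and in random order. A surgeon may also see a fault and leave it, since suboptimal is judged on images alone. This stands: it reduces the bias and makes an open-arm sensitivity of zero unlikely.

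**Another target is legitimate.** Accuracy for faults present at the end of surgery is a coherent question, and pooled conclusive scans answer it. It is not the use of 3D-RX that the trial tests, which is finding faults after an accepted 2D result.

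**The blinded arm is itself selected.** This stands too. Every patient has passed the surgeon's satisfaction on 2D, so a reader should not take the blinded arm as an unselected estimate, least of all for 2D.

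**Conclusion.** The point holds as a bias of known direction and uncertain size. As the article is written, pooled 3D-RX sensitivity is too low as a measure of detecting faults left after an accepted 2D result, unless sensitivity is 1 or the two readings are independent given the fault. With the planning rates and persistent misses the loss is 5.5 points at Se 0.90, 10.9 at 0.80 and 16.0 at the boundary. With half persistence it is about 3 to 8 points over the same range.

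A reader might infer that the plan implies a true sensitivity of 71%, an open-arm sensitivity of zero and a pooled value of 55%. The documents do not support that. The 17% and 5% come from different sources and fix only the product Se·c. The value 71% is the lowest sensitivity compatible with them under this model, and the other two figures follow only if every detected fault is corrected and every miss is repeated.

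Nor does the point touch the primary comparison. Accuracy is the third objective, without a test or target of its own. This is an inexpensive improvement to a non-primary analysis, best settled before results are seen.

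**What to change.** In Primary and secondary endpoints and in Data analysis:

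- Name the blinded arm as the primary analysis set for sensitivity, specificity and predictive values of 3D-RX, and of 2D-fluoroscopy in the same patients.
- Report the open-arm conclusive scans separately, labelled as residual faults after 3D-guided correction, and do not pool them with the blinded arm.
- State that all estimates, including those from the blinded arm, are conditional on a result that the surgeon had already accepted on 2D. The 2D-versus-3D contrast is then read as added yield after that acceptance.

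No new data are needed. Most of the information on sensitivity is kept, about 21 of 27 expected suboptimal cases per joint. The price is the wider intervals shown above, proportionally greater for specificity because about half of the scans are set aside.
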